## Abstract

**Introduction:**

Chronic malnutrition is a serious problem in southern Angola with a prevalence of 49.9% and 37.2% in the provinces of Huila and Cunene, respectively. The MuCCUA (Mother and Child Chronic Undernutrition in Angola) trial is a community-based randomised controlled trial (c-RCT) which aims to evaluate the effectiveness of a nutrition supplementation plus standard of care intervention and a cash transfer plus standard of care intervention in preventing stunting, and to compare them with a standard of care alone intervention in southern Angola. This protocol describes the planned economic evaluation associated with the c-RCT.

**Methods and analysis:**

We will conduct a cost-efficiency and cost-effectiveness analysis nested within the MuCCUA trial with a societal perspective, measuring programme, provider, participant and household costs. We will collect programme costs prospectively using a combined calculation method including quantitative and qualitative data. Financial costs will be estimated by applying activity-based costing methods to accounting records using time allocation sheets. We will estimate costs not included in accounting records by the ingredients approach, and indirect costs incurred by beneficiaries through interviews, household surveys and focus group discussions. Cost-efficiency will be estimated as cost per output achieved by combining activity-specific cost data with routine data on programme outputs. Cost-effectiveness will be assessed as cost per stunting case prevented. We will calculate incremental cost-effectiveness ratios comparing the additional cost per improved outcome of the different intervention arms and the standard of care. We will perform sensitivity analyses to assess robustness of results.

**Ethics and dissemination:**

This economic evaluation will provide useful information to the Angolan Government and other policymakers on the most cost-effective intervention to prevent stunting in this and other comparable contexts. The protocol was approved by the República de Angola Ministério da Saúde Comité de Ética (27C.E/MINSA.INIS/2022). The findings of this study will be disseminated within academia and the wider policy sphere.

**Trial registration number:**

ClinicalTrials.gov Registry (NCT05571280).

STRENGTHS AND LIMITATIONS OF THIS STUDYThis protocol will contribute to the growing evidence regarding cost-effective and cost-efficient multisectoral interventions to prevent chronic malnutrition.The study design draws on a comprehensive and broad cost analysis based on diverse data sources such as trial data, community-level surveys, staff interviews, interviews and focus group discussions with participants, and detailed programme expenditures.The economic evaluation design will allow societal, participant, household and provider costs to be disaggregated.Community-based trials pose methodological challenges in terms of data collection and participant follow-up especially in these rural and remote settings of southern Angola.The economic evaluation will be conducted in the context of a research project, and costs could be influenced by the research component in ways that cannot be seen or corrected for.

## Background

### Burden of child undernutrition

Stunting or chronic malnutrition is the impairment of growth and development that children experience due to malnutrition, repeated infections and inadequate psychosocial stimulation.^1^ Stunting in early life, particularly in the first 1000 days, from conception through the first 2 years of life, has adverse physical and functional consequences in the child including higher risk of morbidity and mortality, lower educational attainment and cognition, lower adult earnings, loss of productivity, and when accompanied by excessive weight gain in childhood, increased risk of nutrition-related chronic diseases in adulthood.^2^ Stunting affects 149.2 million children under 5 years of age. The number of children with stunting is declining in all regions except Africa.^3^

In Angola, the level of chronic malnutrition is high, with 38% of children being stunted and 5% of children being acutely malnourished nationally (Demographic and Health Survey 2016–2017).^3^ According to UNICEF, 3.8 million people in Angola face food and nutrition insecurity due to climate shocks.^4^ Recurrent drought, reduced agricultural and livestock production, crop failures, high food prices and the proliferation of infectious diseases all contribute to compromising maternal and infant nutrition and health.^5 6^ The southwestern provinces of Angola have been most severely affected. In the provinces of Cunene and Huila, the latest Integrated Food Security Phase Classification analysis revealed that over 1.3 million people are estimated to be experiencing high levels of acute food insecurity with more than 50% of their total population in crisis or emergency levels between April 2021 and March 2022.^6^ The situation has deteriorated during the lean season as food reserves were depleted, drought conditions continue to be exacerbated by erratic below-average rainfall and the humanitarian response has proven inadequate to address the most urgent needs.^7^ Further, a Standardised Monitoring and Assessment of Relief and Transitions Survey conducted in 2019 in selected municipalities of Huila and Cunene reported a prevalence of global acute malnutrition of 11% in both provinces, and a stunting prevalence of 49.9% and 37.2% in the provinces of Huila and Cunene, respectively.^8^

Due to the severity of the situation, there is a need to improve the nutritional status of this population. In relation to stunting, there is growing evidence that nutrition-specific interventions such as small-quantity lipid-based nutrient supplementation (SQ-LNS) have benefits on child growth.^9^ The positive effects of SQ-LNS on growth was validated by a meta-analysis that provided evidence of this effect at reducing stunting or wasting in a variety of contexts, recommending to policymakers its inclusion in intervention packages.^10^ There is also evidence that nutrition-sensitive interventions, for example, cash transfers, could improve nutrition and health outcomes and accelerate reductions in stunting.^11 12^ The Crescer Project aims to address stunting in southern Angola by implementing a multisectoral approach with both a nutrition-specific and a nutrition-sensitive intervention.

### Mother and Child Chronic Undernutrition in Angola trial

The Crescer Project is an operational research programme on the prevention of chronic malnutrition in the southern Angolan provinces of Huila and Cunene. It is embedded in the FRESAN (Fortalecimento da Resiliência e da Segurança Alimentar e Nutricional em Angola) Programme, funded by the European Union (European Development Funds) to strengthen resilience and food and nutrition security in southern Angola. The Crescer Project implements the MuCCUA (Mother and Child Chronic Undernutrition in Angola) trial, a three-arm community-based cluster randomised controlled trial of non-inferiority which aims to evaluate the effectiveness and cost-effectiveness of a nutrition supplementation plus standard of care intervention and a cash transfer plus standard of care intervention compared with a standard of care alone intervention in preventing stunting in children at 24 months in Huila and Cunene. Pregnant women and their newborn children are target recipients of either arm: the comparator arm receives standard of care alone, the second arm receives standard of care plus nutrition supplementation with SQ-LNS and a family food ration, and the third arm receives standard of care plus unconditional cash transfers. Community and Health Development Agents (ADECOS) implement the interventions following Angolan Government protocols.^13^ The primary outcome is prevalence of stunting in children. The MuCCUA trial is described in detail elsewhere.^14^ The purpose of this protocol paper is to fully describe the methodology for the economic evaluation of the trial.

### Economic evaluations of multisectoral interventions to prevent child stunting

Delivering multisectoral interventions combining nutrition-specific and nutrition-sensitive interventions during the first 1000 days of life is key to prevent chronic malnutrition and to improve early child growth.^15^ Reduction of stunting requires improvements in food and nutrition security, education, water, sanitation and hygiene interventions, health, the status of women and poverty reduction.^2^ Maternal and child interventions such as nutritional supplementation with SQ-LNS,^10 16–18^ cash transfers,^12 19 20^ vitamin A supplementation and behaviour change communication have shown promising results in preventing chronic malnutrition.^21 22^ However, evidence on the effectiveness of combining them in multisectoral programmes is scarce.^23^

In order to advocate for further investment on these multisectoral programmes, there is a need to provide knowledge not just on their effectiveness but also on their costs,^24^ as funding agencies are increasingly requesting implementers to include economic evaluations in their proposals.

The body of economic evidence supporting nutrition programmes is growing,^15^ but it is still limited especially for low-income and middle-income countries (LMICs)^25 26^ and for multisectoral nutrition interventions.^15^

Multisectoral programmes including health, nutrition, cash and behaviour change communication interventions pose challenges for economic evaluations due to their heterogeneity. First, studies with interventions delivered in different sectors can be difficult to compare due to differences in the outcomes and costs included.^27–30^ Second, the perspective chosen for the economic evaluation poses another challenge for interpretation and comparison of findings between studies because of the different sets of costs included.^25 31 32^ Third, economic evaluation objectives differ greatly between studies as some aim to prioritise policies and funds, and different studies may aim to inform different decision-makers.^28^

There are published studies on the costs of complex interventions including nutrition supplementation^33 34^ or cash transfer interventions,^11 35^ but to the best of our knowledge, there are no studies comparing the costs of these two interventions within the same project, as this study does.

Finally, a recent review on cost analysis of nutrition interventions on LMICs highlighted the need to standardise methods and reporting in economic evaluations in order to facilitate interpretation and provide a means for comparing costs and cost-effectiveness of interventions.^36^ The initiative SEEMS-Nutrition (Strengthening Economic Evaluation for Multisectoral Strategies for Nutrition) has developed a common approach guide to measure the costs and benefits of multisectoral nutrition strategies^37^ that we have followed.

The proposed economic evaluation of the MuCCUA trial aims to address the challenges mentioned above by assessing the cost-efficiency and cost-effectiveness of the interventions following the SEEMS guide. The perspective used will be societal including all costs of the interventions regardless of who incurs them.

Thus, we hope to contribute to the scarce literature on the cost-efficiency and the cost-effectiveness of implementing multisectoral nutrition interventions including both nutrition-specific and nutrition-sensitive interventions, with a standardised methodology in an LMIC real-world setting located in southern Angola.

### Aim and objectives

The aim of the MuCCUA trial economic evaluation is to use a societal perspective to estimate the costs, and evaluate the cost-efficiency and cost-effectiveness of three interventions (standard of care alone, standard of care plus nutritional supplements and standard of care plus cash transfers) in reducing stunting in children under 2 years of age from poor and very poor households in the southern provinces of Cunene and Huila in Angola.

The specific objectives of the economic evaluation are the following:

To estimate the costs of setting up and implementing each of the MuCCUA interventions.To calculate costs incurred by the intervention participants and their families as a result of the interventions.To estimate the cost-efficiency of each of the three interventions as cost per woman, child and household reached.To estimate the cost-effectiveness as cost per case of stunting averted by comparing incremental costs and incremental changes in the outcomes of the interventions, compared with the standard of care.

In addition to the above objectives, heterogeneity analysis of the MuCCUA interventions will be assessed to evaluate how the costs and consequences of the interventions are distributed among different subgroups of the study population.

## Methods

### Study design

A cost-efficiency and cost-effectiveness analysis of the MuCCUA trial, a community-based cluster randomised trial that compares three interventions to prevent children’s stunting taking place between October 2022 and February 2025. We will estimate the total and incremental costs of the interventions prospectively from a societal perspective, measuring programme, provider, participants and household costs.

### Patient and public involvement

Community leaders (locally named ‘sobas’) and the community were involved at the early stages of the research with discussions about the outcomes and the interventions. Then, ADECOS were selected by their own communities only after fulfilling certain technical and capacity criteria. Sobas, communities and ADECOS were involved in the cluster randomisation. Methods of recruitment were informed by discussions with community activity assistants and ADECOS through a focus group session. All women from selected randomised communities included were identified and informed of the study by ADECOS.

Pregnant women and their families were not involved in setting the research question or the outcome measures. The project is promoting understanding and dissemination of key messages around the interventions to motivate community involvement during and beyond the study. A feedback/suggestions mechanism for participants and communities has been implemented as well.

At the end of the study, results will be shared and discussed with participants, their families and communities through dedicated workshops. Results and all the knowledge generated should promote change at community, regional and national level in policies and practices.

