The study participants are pregnant women confirmed by pregnancy test and over 16 years of age, and their newborn children. The target population of the interventions is the household in which the pregnant woman and their children live. In the case of having more than one pregnant woman within the household, all women who accept to participate will be included. We consider households to be the person or group of persons, with or without kinship relationships, who have been habitually living under the same roof for at least 6 months or less but with the intention of staying in the residence for the next 6 months and share food and/or other vital needs such as water, cooking and eating utensils and hygiene products. Informed cluster-level consent was sought from village leaders, sobas, to participate in the trial before randomisation. After acceptance to participate in the study through the informed consent, mothers and their children are followed up from the time of pregnancy at the time of recruitment until the child is 24 months old.

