### Trial design

In the MuCCUA trial, a total of 36 purposively selected clusters (the selection of which is described below), with an estimated population of around 55 000, were randomised to the three trial arms with six clusters per arm in Huila province, and six clusters per arm in Cunene province. Two municipalities (admin 2) were selected per province (admin 1) with one commune (admin 3) per municipality (total two communes per province). In the province of Huila, the commune of Libongue (municipality of Chicomba) and the commune of Jamba Sede (municipality of Jamba) were selected. In the province of Cunene, the commune of Otchinjau (municipality of Cahama) and the commune of Mupa-Mukolongodjo (municipality of Cuvelai) were selected. The cluster unit is typically a village or neighbourhood and any nearby hamlets within each commune or, in the case of large neighbourhoods, a distinct part of it that is similar in population size to the unit. The randomisation, which took place in September 2022, was stratified by cluster.

The inclusion criteria for clusters were being considered as one of the municipalities prioritised by the FRESAN Programme and having a multidimensional poverty level 4 or 5 according to the Instituto Nacional de Estatística classification,^39^ not currently having or planned to have in operation other interventions offering monetary or nutritional transfers, acceptance by the municipal and traditional authorities, accessible in a 4×4 vehicle and having a reference health post with reference health personnel.

Recruitment and baseline survey started in October 2022 and will continue until March 2023. Implementation started at recruitment and is planned to end in November 2025. A total of 1440 pregnant women and their newborns, 480 in each arm, are enrolled. Primary efficacy analyses will be performed when the participant’s children have completed a total of 24 months of follow-up. A full description of the intervention design within the MuCCUA trial is described in detail elsewhere.^14^ A brief description of the interventions is presented in the following sections.

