#### Cost-effectiveness analysis

Economic evaluation will be conducted as a within-trial analysis using the intention-to-treat results, and will be presented in terms of incremental cost-effectiveness ratios (ICERs), calculated as the difference in total costs of standard care only (or comparator) versus nutritional supplementation or cash transfer divided by the difference in mean effects of each intervention versus control. As mentioned previously, ICERs will be calculated in terms of cost per stunting case prevented among children at 24 months old if there is a statistically significant difference in the outcome between intervention study arms.

The ICER will be calculated to compare the additional costs per improved outcome achieved in interventions, including nutritional supplements or cash transfers, compared with the standard of care intervention. Where feasible, we will disaggregate costs for different time frames, including start-up versus recurrent costs.

Sensitivity analysis will be performed to determine the extent to which the results of the analysis might change given plausible variation in study parameters related to cost drivers and stunting rates. To obtain an estimate of how costs could vary, a range of costs will be calculated based on different scenarios such as local costs scenario, product price or coverage. Univariate and multivariate probabilistic sensitivity analyses will assess effect of the main cost drivers on the results.

All costs will be presented in 2022 Angola kwanzas and in US dollars (USD). We will use the average monthly exchange rate for the year of cost data collection to convert costs into USD. Any costs encountered in the past will be inflated using the local gross domestic product deflator of Angola, before converting to USD. In addition, some expenses will be in euros and we will use the average exchange rate for the year of cost data collection to convert costs into USD. All costs will be adjusted for inflation using the Angolan Consumer Price Index and will be converted to 2022 USD using the purchasing power parity conversion factor for Angola. Moreover, the costs will be discounted using a standard discount rate of 3%, as recommended by WHO-CHOICE^48^ and the Gates/IDSi Reference Case for Economic Evaluation.^49^

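### Women were found by ADECOS over six months after an open cluster randomisation, with cash or food in two arms only, so who enrols and when can differ by arm, and the planned intention-to-treat contrast does not correct for it

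*Protocol article*

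**What the plan says.** The sequence is stated in the protocol article.

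- Allocation: "The randomisation, which took place in September 2022, was stratified by cluster" (Trial design). It was not hidden locally: "Sobas, communities and ADECOS were involved in the cluster randomisation" (Patient and public involvement).
- Recruitment: "Recruitment and baseline survey started in October 2022 and will continue until March 2023" (Trial design).
- Who finds the women: "All women from selected randomised communities included were identified and informed of the study by ADECOS" (Patient and public involvement). The same cadre delivers the programme: "Community and Health Development Agents (ADECOS) implement the interventions following Angolan Government protocols" (section on the MuCCUA trial).
- Consent: "Informed cluster-level consent was sought from village leaders, sobas, to participate in the trial before randomisation" (Study setting and population). Individual consent comes at recruitment. No individual step is stated to precede the draw.
- What enrolment brings: 13 855 or 10 855 kwanzas a month in the cash arm; SQ-LNS and a family food ration in the nutrition arm; standard of care alone in the control arm (MuCCUA interventions). Raising participation is among the stated purposes of the food basket.
- Analysis: "Economic evaluation will be conducted as a within-trial analysis using the intention-to-treat results" (Cost-effectiveness analysis).

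**The concern.** In a cluster trial, randomisation balances clusters. It balances the women inside them only if entry does not depend on the arm. Here the people who identify women know the arm, the communities know it, and enrolment is worth far more to a family in two arms than in the third. Women in the cash and food arms have a reason to come forward, and to do so early in pregnancy, that control women lack.

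Two things could then differ by arm: the underlying stunting risk and household circumstances of those enrolled, and the stage of pregnancy at entry. The first distorts the stunting contrast, which is the denominator of the ICER. It also distorts the participant and household part of the cost, since travel and time costs depend on who the women are and where they live. The second matters because implementation starts at recruitment, so the date of entry sets the length of prenatal exposure. Intention-to-treat does not help, because the selection happens before a woman enters the analysis set.

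**Working it through.** **1. Order of events.** Randomisation was in September 2022 and recruitment ran from October 2022 to March 2023. Every individual enrolment in the stated window therefore follows an allocation in which leaders, communities and ADECOS took part.

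**2. Layout (Trial design).** 36 clusters / 3 arms = 12 per arm. 1440 women / 3 = 480 per arm. 480 / 12 = 40 women per cluster on average. These figures agree with one another. The 480 cannot be re-derived from the article, which omits several inputs to that calculation, and nothing here depends on it.

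**3. Strength of the incentive.** Against the stated minimum salary of 35 000 kwanzas a month, the cash is 13 855 / 35 000 = 40% for larger households and 10 855 / 35 000 = 31% for smaller ones. In the control arm it is zero.

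**4. Room for selection.** Population per cluster is 55 000 / 36 = about 1528. The birth rate is not given, so assume 30 to 45 per 1000 a year and 5 to 7 months of detectable pregnancy. Eligible women per cluster over the six-month window = annual births x (detectable months + 6) / 12.

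- Low end: 1528 x 0.030 = 45.8 births; 45.8 x 11/12 = 42.0 women; 40 / 42.0 = 95%.
- High end: 1528 x 0.045 = 68.8 births; 68.8 x 13/12 = 74.5 women; 40 / 74.5 = 54%.

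The quota therefore needs about 54-95% of eligible women. At the upper figure there is little room for selection; at the lower figure there is a lot. A fixed 480 per arm equalises numbers, not composition or timing.

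**5. What selection could do to the stunting contrast.** Bias = (share of one arm that differs because of selection) x (difference in stunting risk). Both inputs are assumed.

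- Smallest case: 0.10 x 0.05 = 0.5 points.
- Middle case: 0.20 x 0.10 = 2.0 points.
- Largest case: 0.30 x 0.15 = 4.5 points.

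The article powers the trial for a 13% reduction without saying whether this is absolute or relative. Read as 13 points, the bias is 0.5/13 = 4% to 4.5/13 = 35% of the effect. With incremental cost held fixed, the ICER is multiplied by between 13/(13 + 4.5) = 0.74 and 13/(13 - 4.5) = 1.53. Read as relative to the quoted provincial prevalences, the effect is 0.13 x 37.2 = 4.8 to 0.13 x 49.9 = 6.5 points, and the same bias would be a larger share. The direction is not known: women drawn in by a transfer could be at higher or lower risk than those who would enrol without one.

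**6. Cost side.** Assuming payment from enrolment, each month of earlier entry in the cash arm adds 13 855 kwanzas (US$31.5) to the cost of a larger household. That money is really spent, so it is a programme cost and not a bias. The part open to bias is the participant and household cost, through the mix of women enrolled.

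**The case against.** Four objections have force.

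- **Earlier uptake may be a real consequence of the programme.** Transfers delivered are a true cost, and added prenatal exposure is a true effect. This stands. A reader might compare entry at month 2 with entry at month 8 of pregnancy (31 against 25 months of cash, a ratio of 1.24) and call the 24% gap a bias. It is not: it compares two hypothetical households in one arm, not two arms, and both costs would be genuine.
- **Gestational age at enrolment may itself respond to allocation.** Adjusting the main contrast for it could remove part of the intervention's own cost and effect. This stands, and it limits such adjustment to a sensitivity analysis.
- **The text says less than it first appears to.** A reader might infer that women who move into a cash or food village after the draw qualify, because a household may include people resident "for at least 6 months or less but with the intention of staying in the residence for the next 6 months". That wording defines a household; it is not an eligibility rule for women. Nor does the article say that ADECOS took consent, only that they identified and informed women. It says that all women were identified, which points to active case-finding and softens the concern. It does not remove it: identification is not enrolment, and those identifying knew the arm.
- **The main trial protocol, not shown here, may contain safeguards.** It may, so no weight is put on what this article omits. The point rests on the sequence, roles and incentives that it states.

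**Conclusion.** The concern holds as a risk of recruitment bias after allocation. Open allocation, recruitment afterwards through the implementing agents, and unequal incentives are all stated, and the intention-to-treat contrast does not correct for who enrolled. The documents do not show that bias occurred, how large it is, or which way it runs. The range of 0.5-4.5 points, and the ICER factor of 0.74-1.53 on an absolute 13-point effect, are illustrations that rest on the assumed share and risk difference; the 54-95% quota figure rests on assumed birth rates. The point warrants a change to the analysis and reporting text, not to the design.

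**What to change.** In the Cost-effectiveness analysis section:

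- Present the stunting contrast, and the participant and household cost contrasts, adjusted for baseline maternal and household characteristics from the existing baseline survey, beside the unadjusted results. Because that survey follows allocation, choose characteristics that allocation could not have changed.
- Add, as a sensitivity analysis only, either adjustment for gestational age at enrolment or restriction to women already pregnant at the September 2022 randomisation (and already resident in the cluster, if residence data exist). Give the reason for its status: enrolment timing may be affected by allocation.

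In reporting, give by arm the number of women identified, the number enrolled and gestational age at enrolment. In the strengths and limitations list, name open recruitment after randomisation.

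The cost is a little more analysis and some loss of precision in the restricted analysis, which drops women who conceived after the draw. Neither sensitivity analysis removes selection among the women who remain, so the limitation should be stated whatever they show.
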